### Study design and setting

ENFORCER is an interventional parallel-group randomized controlled trial. Recruited participants will be randomized 1:1 to the intervention or control group using simple computerized randomization obtained at the time of enrolment.

The 38 collaborating institutions will refer potentially eligible patients to the coordinating centre for participation, but also caregivers and self-referral are allowed.

All outpatients who meet the eligibility criteria will be recruited after discharge from hospital, regardless of geographic location.

A trained neuropsychologist, blinded to patient group allocation, will conduct the clinical assessments. All professionals involved in data management and analysis will also be blinded to group allocation. Unblinding will be possible only at the request of the Data Safety and Monitoring Board (DSMB).

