### Intervention

The program is designed to be self-operating and is delivered through a secure web application created exclusively for this research (https://www.studioenforcer.it/EN).

It is designed to improve cognitive abilities, offer emotional and affective support, and aid in physical rehabilitation.

The one-year program will begin with six months of weekly educational sessions and interactive tasks, followed by six months of occasional reminders to exercise.

To effectively address the most affected areas, patients with cognitive impairment will begin with cognitive enhancement, those with emotional problems will begin with emotional support, and those with both will be randomly assigned to receiving emotional support first, followed by cognitive enhancement or vice versa.

After the initial presentation, all educational and interactive materials will be available for further practice. Physical rehabilitation education will be provided concurrently to ensure a gradual progression towards physical goals.

Caregivers of participants in the study will receive customized education via the web application. Concurrent medical, psychological, or physical therapies are permitted and will be observed at all follow-up stages of the study.

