### Control group

Patients randomized to the control group will be followed up by their primary care physician (usual care). They will be asked to complete the diaries and all the assessments at the same scheduled follow-up visits and as the intervention group.

Throughout the study, participants will be allowed to receive concurrent pharmacological, psychological, or physical treatments. The concurrent use of medications such as antidepressants, anxiolytics, antipsychotics, opiates, and other analgesics, as well as any form of psychotherapy or physiotherapy, will be carefully recorded at the scheduled visits.

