### Sample size

The sample size was defined assuming a 25 % difference in the primary outcome (the proportion of patients free of emotional or cognitive disorders at 12 months after enrolment, i.e. HADS<8 and/or TICS>31), i.e. 55 % in the intervention group vs. 30 % in the control group. A total sample size of 96 patients (48 per group) was estimated to be required to reject the null hypothesis of equal proportions in the two groups with 80 % power, an alpha error of 0.05, and a 1:1 randomization. Considering a dropout rate of 30 %, the final sample size was set at 137.

Based on the historical data of the participating centres, an annual flow of 350 patients is expected. According to literature reports that the prevalence of anxiety and depression symptoms is approximately 30 % of OHCA survivors^28^ and cognitive impairment is up to 50 %,^2^ we estimate that about 60–70 % (210–245 patients/year) of patients will be eligible for enrolment, therefore, the full sample size should be reached within 12 months from the beginning of the study. In case of slow recruitment, an extension of the enrolment period up to 24 months will be requested.

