### Data collection and statistical analysis plan

Questionnaires and diaries completed by participants will be collected directly via an electronic case report form (eCRF) integrated into a web application. The same application will facilitate data entry for the researcher conducting the observer-rated assessments, using a distinct user interface with unique login credentials. To ensure data quality, the rater will be trained in clinical assessment and completion of the observer-rated questionnaires. Participants will be automatically checked for data completeness, and they will receive regular reminders to ensure timely data entry.

The proportions of patients without cognitive or emotional symptoms 12 months after enrolment will be compared between groups using the z-test. A modified intent-to-treat approach will be used, including in the analysis patients who received at least one the web-based treatment session or standard care. To manage missing/incomplete data and to address a possible selection bias related to the modified intent-to-treat approach we will focus on the possible distribution of the missing data given the observed data. In order to do so, we will determine whether the distribution of patients’ unseen observations at the final visit, given their observations at previous visits and baseline, is different from that seen among the patients who have no missing data. To estimate the intervention effect at the end of the trial, we will make assumptions about how the patterns differ in the two groups of patients. We will then estimate the intervention effect amongst those who do, and do not have, missing data, which has to be averaged, to arrive at the overall estimate of the effect of intervention.^29^

Secondary outcome measures will be compared between the two groups using the *t*-test or Mann-Whitney *U* test according to their frequency distribution.

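### The modified intention-to-treat set can in practice exclude only intervention patients, for behaviour after randomisation, so the primary comparison may be biased in either direction

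*Protocol article*

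**What the plan says.** In the protocol article, under Data collection and statistical analysis plan, the primary proportions "will be compared between groups using the z-test". The analysis set is a modified intention-to-treat set, "including in the analysis patients who received at least one the web-based treatment session or standard care".

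Two other sections determine how that rule works in each arm:
- Control group: "Patients randomized to the control group will be followed up by their primary care physician (usual care".
- Intervention: "The program is designed to be self-operating and is delivered through a secure web application".

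The article sees a risk here. It introduces its missing-data method partly "to address a possible selection bias related to the modified intent-to-treat approach". The method compares unseen final-visit observations with those of patients who have complete data, given baseline and earlier visits, and makes assumptions about how the two patterns differ. Then: "We will then estimate the intervention effect amongst those who do, and do not have, missing data, which has to be averaged". The article names no analysis of all randomised patients.

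**The concern.** The two halves of the inclusion rule are not equivalent. A control patient meets it by being left to ordinary follow-up. An intervention patient meets it only by opening a session. Whether a patient opens one is decided after allocation, and it is plausibly related to mood and cognition, which are the domains that define both entry and the primary endpoint.

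Randomisation protects the comparison only while the groups analysed are those it formed. Removing a self-selected part of one arm, while its counterparts in the other arm cannot be identified and stay in, gives up that protection in the primary analysis.

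It also shifts the question. The stated aim is effectiveness against usual care. For a programme that patients run themselves, failure to start is part of effectiveness.

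**Working it through.** **The plan's own figure.** The document gives no figure for never-starters, so there is none to reproduce on that point. The design figures used below are "55 % in the intervention group vs. 30 % in the control group", 48 per group, 137 in total. With pooled variance and no continuity correction, n per group = [z_α√(2·0.425·0.575) + 0.842√(0.55·0.45 + 0.30·0.70)]² / 0.25². This gives 48 with z_α = 1.645 (one-sided 0.05) and 61 with z_α = 1.960 (two-sided). Dropout: 96/0.70 = 137.1. The stated 96 therefore matches a one-sided calculation. Sidedness is not stated and is a separate matter, but it affects the power figures in step 3.

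**Step 1: size of the bias when there is no true effect.** Let p be the success rate in the whole intervention arm, f the share who never open a session, and q the success rate in that share. Among starters the rate is r = (p − f·q)/(1 − f), and the bias is r − p. I take p = 30% in both arms. The values of f and q are assumptions.

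Example, f = 20%, q = 10%: r = (0.30 − 0.02)/0.80 = 0.35, a bias of +5.0 points.

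**Step 2: type I error.** Two-sided pooled z-test at 0.05, normal approximation, 68 randomised per arm, no other loss. For the example, n₁ = 68 × 0.80 = 54.4 and n₂ = 68. The pooled rate is (54.4·0.35 + 68·0.30)/122.4 = 0.322. The standard error is 0.0850 under the null and 0.0853 for the actual rates. P(reject) = 1 − Φ[(1.96·0.0850 − 0.05)/0.0853] + Φ[(−1.96·0.0850 − 0.05)/0.0853] = 0.091.

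| Never start (f) | q = 10% | q = 30% | q = 50% |
|---|---|---|---|
| 10% | +2.2 points, 5.9% | 0, 5.0% | −2.2 points, 5.9% |
| 20% | +5.0 points, 9.1% | 0, 5.0% | −5.0 points, 9.2% |
| 30% | +8.6 points, 16.2% | 0, 5.0% | −8.6 points, 17.1% |

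Exact enumeration of the same test, with 54 starters (20% non-start) against 69 controls, also gives about 9%, 5% and 9%. The inflation depends on numbers analysed. Starting from 48 per arm, exact enumeration gives 7.5% for f = 20%, q = 10% and 13.7% for f = 30%, q = 10%.

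**Step 3: when the treatment works only in those who start.** Suppose starters reach 55% and never-starters stay at the 30% control rate. The modified set shows 55 − 30 = 25 points. The effect of assignment is 0.90·55 + 0.10·30 − 30 = 22.5 points at f = 10%, and 0.80·55 + 0.20·30 − 30 = 20 points at f = 20%. With 48 per group, one-sided power falls from 80.5% to 72.9% and 64.2%. Two-sided power falls from 70.4% to 61.3% and 51.6%.

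**Step 4: does the planned safeguard close the gap?** The method is aimed at final-visit observations that were not seen. Never starting is a different condition. A never-starter who completes the 12-month HADS and TICS has nothing unseen, yet falls outside the set. The text does not say that this patient, or a never-starter without an outcome, enters the averaged estimate.

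**The case against.** **Direction.** A reader might infer that the rule favours the intervention. The documents do not support that as a fact, because nothing in them says who will fail to start. If non-starters are patients who feel recovered, the sign reverses, and if they succeed at the control rate there is no bias under the null.

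**Size.** No non-start share is given. Eligibility requires Internet literacy, which may keep it small, and the calculation ignores the planned 30% dropout. The type I figures are therefore illustrations and not forecasts.

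**The plan already deals with it.** The article names the selection bias as a target of its missing-data method and does not expressly confine that method to included patients. A reader might infer that the method cannot restore the excluded patients. That goes too far. The fair statement is that the article does not clearly say it does, least of all for those with an observed outcome. A condensed article may leave modelling detail to a full plan, but here the set itself is stated.

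**Blinding.** A reader might also infer that a log-in rule reveals allocation, against the statement that "All professionals involved in data management and analysis will also be blinded to group allocation". This is not specific to the rule. Table 3 lists log-in counts and hours on the site as adherence indicators in any case, and a ready-made inclusion flag could be supplied to the analysts.

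**Limited gain.** HADS is self-reported through the web application, so some non-starters may have no 12-month value under either set. That stands. However, opening a session and completing a questionnaire are different acts, and both arms use the application for questionnaires.

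**Conclusion.** The point holds in a limited form. The primary set depends on post-randomisation behaviour that in practice only intervention patients can fail to show. That every control qualifies is an inference from the description of usual care, but a sound one.

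The resulting bias is of unknown sign and size. A shift towards benefit is plausible, if non-starters do worse or if the effect is confined to starters, but it is not established. With 20% non-start the illustration runs from +5 to −5 points, and two-sided type I error reaches about 9% at either end. This rests on an assumed non-start share, assumed success rates among non-starters, 30% success in both arms and no other loss.

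An avoidable bias of unknown direction in the primary comparison is reason enough to change the set. The acknowledgement in the article does not remove it as written.

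**What to change.** 1. Define the primary analysis set as all randomised patients, analysed in the allocated arm whatever their log-in activity.
2. Keep seeking the 12-month HADS and TICS from patients who never open a session.
3. State that the planned missing-data model is applied to this full set and covers any non-starter without an outcome. A non-starter with an observed outcome is analysed with that outcome.
4. Keep the at-least-one-session set as a labelled supplementary analysis.

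**Cost.** This is mainly a wording change, since both arms already have the same scheduled assessments. Two consequences should be accepted openly. The estimated effect may be diluted, as in step 3 of the working, if the planned 55% describes starters; if it already describes everyone assigned, the planned difference is unchanged. Some non-starters may lack a web-entered HADS, so their contribution will rest on the missing-data model.

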**Methods:**

ENFORCER is a multicentre, parallel group randomized controlled trial involving OHCA survivors aged 18–80 years with cognitive impairment or anxiety/depression measured through validated instruments.

Participants will be randomized 1:1 to the intervention or the control group. The intervention group will receive a one-year program via a secure web application, offering cognitive, emotional, and physical rehabilitation support. The control group will receive standard care.

The primary outcome is the difference in the proportion of patients without cognitive or emotional symptoms between the two groups after one year.

Secondary outcomes include changes in the level of patients’ cognitive and emotional symptoms, quality of life, sleep quality, sexual interest and satisfaction, and caregivers’ burden, quality of life, sleep quality and emotional symptoms in the two groups.

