### Aims

The primary aim is to evaluate the effectiveness of internet-based lifestyle interventions on anxiety, depression and cognitive impairment in OHCA survivors with good neurological recovery compared to usual care. The primary outcome is the difference in the proportion of patients without cognitive or emotional symptoms between the two groups one year after enrolment.

The first secondary aim is to evaluate the effectiveness of internet-based lifestyle interventions on HRQoL, behavioural efficiency, and sleep quality in OHCA survivors with good neurological recovery. Outcomes will be assessed at baseline and at 1-, 3-, 6-, and 12-months post-randomization with continuous log-data collection for user engagement.

Other secondary aims include the assessment of caregivers’ HRQoL, anxiety and depression, sleep quality and burden, the validation of the Italian version of the Sexual Interest and Satisfaction Scale (SISS) and the identification of factors associated with anxiety and depression in OHCA survivors with good neurological recovery.

Primary and secondary objectives and outcome measures are listed in Table 1.

**Table 1 t0005:** Outcomes and Outcome Measures of the ENFORCER study.

Outcome	Outcome measure
Primary endpoint	
Effectiveness of internet-based lifestyle interventions on anxiety, depression and cognitive impairment	Proportion of patients without cognitive or emotional symptoms (HADS<8 and TICS>31) one year after enrolment
Secondary endpoints	
Effectiveness of internet-based lifestyle interventions on patients’ health-related quality of life, sleep quality, behavioral efficiency, sexual function, and on caregivers’ burden, health-related quality of life, sleep quality and emotional symptoms	Short Form Health Survey 12 (SF-12) Pittsburgh Sleep Quality Index (PSQI) Neurobehavioral rating scale (NRS) Patient Competency Rating Scale (PCRS) Sexual Interest and Satisfaction Scale (SISS) Zarit Burden Inventory (ZBI)
Factors associated with emotional or cognitive impairment	Presence or absence of the cognitive or emotional symptoms at enrollment (t_-1_)
Italian validation of the Sexual Interest and Satisfaction Scale	−

Abbreviations: HADS – hospital anxiety and depression scale; TICS – telephone interview for cognitive status.

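### Secondary outcomes are compared by unadjusted two-group tests with no baseline adjustment, tested quantity or visit stated, which loses precision whether final values or changes are tested

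*Protocol article*

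**What the plan says.** All secondary outcomes are covered by one sentence in the protocol article, under Data collection and statistical analysis plan: "Secondary outcome measures will be compared between the two groups using the" t-test or the Mann-Whitney U "test according to their frequency distribution". It names no covariate, longitudinal model or visit.

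Under Aims, the article states: "Outcomes will be assessed at baseline and at 1-, 3-, 6-, and 12-months post-randomization".

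The abstract describes the outcomes as changes: "Secondary outcomes include changes in the level of patients’ cognitive and emotional symptoms, quality of life, sleep quality" and further scales. The secondary row of Table 1 lists SF-12, PSQI, NRS, PCRS, SISS and ZBI, but no patient HADS or TICS score.

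The missing-data paragraph comes after the primary z-test and before the sentence on secondary outcomes. It describes a method that models unseen final-visit values "given their observations at previous visits and baseline". Its stated purpose is "To estimate the intervention effect at the end of the trial". It does not say whether it covers the secondary outcomes. The Sample size section expects 30% dropout.

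**The concern.** Each repeated scale has a baseline score that predicts the 12-month score, and the stated tests do not adjust for it. Intervals for quality of life, sleep and the other scales will then be wider than the data allow. Randomization is simple and 1:1, so with about 68 patients per arm a baseline mean can differ between arms by chance by about 1.96 × √(2/68) = 0.34 SD (95% range). An unadjusted final-value comparison carries that difference into the estimate.

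Three related matters are left open or fixed badly:

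- **Quantity and visit.** Final value and change are different analyses with different precision. Testing at each visit would give four tests per scale with no lead comparison.
- **Dropout.** A two-sample test on observed 12-month values cannot use the earlier visits of patients who have left.
- **Choice of test.** If the distribution of the data decides between t-test and rank test, the effect measure is unknown until the data are seen and may differ between scales. A rank test gives no mean difference.

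**Working it through.** **The plan's own figure.** No figure is given for the secondary outcomes. The only stated size is for the primary outcome: 48 per group (96 in total), raised to 137. For "55 % in the intervention group vs. 30 % in the control group" at 80% power, the pooled-variance formula gives 48 per group with a one-sided alpha of 0.05 and 61 with a two-sided alpha; that is a separate matter. Inflation: 96 / 0.70 = 137.1, stated as 137. Below, 48 per arm serves only as the number of 12-month completers. Expected dropouts: 0.30 × 137 ≈ 41.

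**Assumptions.** The baseline-to-12-month correlation r is not in the documents; 0.3 to 0.7 is assumed. The illustrative effect is 0.5 SD of the final score. Tests are two-sided at 0.05 with the normal approximation. The SD is taken as equal at both visits, which matters only for the change-score column.

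**Formulas**, relative to a final-value t-test (variance 1):

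- change score: 2(1 − r)
- ANCOVA: 1 − r²
- ANCOVA relative to change score: (1 − r²) / [2(1 − r)] = (1 + r)/2

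| r | ANCOVA / final value | ANCOVA / change score | Per-arm n for a final-value t-test to match ANCOVA at 48 |
|---|---|---|---|
| 0.3 | 0.91 | 0.65 | 48/0.91 = 53 |
| 0.5 | 0.75 | 0.75 | 48/0.75 = 64 |
| 0.7 | 0.51 | 0.85 | 48/0.51 = 94 |

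**Detectable difference** at 80% power with 48 per arm: (1.96 + 0.84) × √(2/48) = 0.57 SD for final values. Multiplying by √(1 − r²) gives 0.55, 0.50 and 0.41 SD with ANCOVA at r = 0.3, 0.5 and 0.7.

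**Power** for 0.5 SD with 48 per arm:

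| r | Final value | Change score | ANCOVA |
|---|---|---|---|
| 0.3 | 69% | 54% | 73% |
| 0.5 | 69% | 69% | 81% |
| 0.7 | 69% | 89% | 93% |

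The unadjusted analyses trade places as r moves through 0.5. ANCOVA is ahead of both throughout the range, so the conclusion does not depend on which quantity the plan means.

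**Dropout.** If the test uses observed 12-month values only, about 41 of 137 patients are left out, along with any scores they gave at 1, 3 and 6 months.

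**The case against.** Several stronger readings are tempting, and the documents do not support them.

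- **That the baseline value is not used at all.** The analysis sentence names a test, not the quantity tested, and the abstract speaks of changes. A t-test on change from baseline fits both places and does use baseline. What stands is that no adjustment is specified and the quantity is unclear.
- **That dropouts' earlier data are discarded.** No visit and no complete-case rule is stated for the secondary outcomes. Visit-by-visit tests would use the earlier data, and the missing-data paragraph might be meant to extend to these outcomes. The loss is therefore conditional on an observed-case test at 12 months.
- **That the unadjusted tests are biased.** Under randomization they are valid, and leaving out baseline costs precision only. Dropout that depends on baseline alike in both arms, with an additive effect, also leaves the completers' difference unbiased. Bias needs dropout that depends on post-randomization scores or differs by arm, or an effect that varies with the score driving dropout.

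Three further limits stand. The size rests on an assumed r, and since patients are selected on HADS and TICS at entry, the correlation for those two scales may lie low in the range. The body of Table 2 is not readable in the text at hand, so it cannot be confirmed that every scale, the ZBI in particular, is collected at baseline and at each visit. And these are secondary outcomes, with no sample-size claim attached.

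It can also be said that covariates and time points belong in an analysis plan that is not shown. That would answer a silent article. This one states the method, and an analysis plan that followed it would inherit the weakness.

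**Conclusion.** The point holds as a loss of precision and an ambiguity, not as a demonstrated bias. The article fixes an unadjusted t-test or rank test, selected by distribution, for outcomes it schedules at baseline and four later visits. For an assumed correlation of 0.3 to 0.7, baseline adjustment removes 9% to 49% of the variance of a final-value t-test, or 35% down to 15% of that of a change-score t-test. The change-score range also assumes equal SDs at the two visits. The loss of about 41 patients' earlier data, and any bias from it, applies only if observed 12-month values alone are tested.

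The absence of patient HADS and TICS scores from the secondary row of Table 1, against the abstract, is a real but minor inconsistency that rests on no assumption. The change is worth making; the primary analysis is not affected.

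**What to change.** 1. For each continuous secondary outcome measured at baseline, specify a baseline-adjusted model: ANCOVA or, where the scale is repeated, a mixed model for repeated measures with arm, visit, arm-by-visit and baseline score.
2. Name 12 months as the visit of interest and report the adjusted mean difference with its 95% CI.
3. For skewed scales, use robust or bootstrap standard errors instead of switching to a rank test on the observed distribution.
4. State whether the missing-data method covers the secondary outcomes. The mixed model uses the earlier visits of patients who leave, under the assumption that dropout depends only on what was observed.
5. Add patient HADS and TICS scores to the secondary outcomes in Table 1, to agree with the abstract.

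The cost is analysis wording and code. No new visits or data are needed for scales already scheduled at baseline.
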